## Abstract

**Background:**

Survival rates from out-of-hospital cardiac arrest (OHCA) remain low, despite remarkable efforts to improve care. A number of ambulance services in the United Kingdom (UK) have developed prehospital critical care teams (CCTs) which attend critically ill patients, including OHCA. However, current scientific evidence describing CCTs attending OHCA is sparse and research to date has not demonstrated clear benefits from this model of care.

**Methods:**

This prospective, observational study will describe the effect of CCTs on survival from OHCA, when compared to advanced-life-support (ALS), the current standard of prehospital care in the UK. In addition, we will describe the association between individual critical care interventions and survival, and also the costs of CCTs for OHCA.

To examine the effect of CCTs on survival from OHCA, we will use routine Utstein variables data already collected in a number of UK ambulance trusts. We will use propensity score matching to adjust for imbalances between the CCT and ALS groups. The primary outcome will be survival to hospital discharge, with the secondary outcome of survival to hospital admission.

We will record the critical care interventions delivered during CCT attendance at OHCA. We will describe frequencies and aim to use multiple logistic regression to examine possible associations with survival.

Finally, we will undertake a stakeholder-focused cost analysis of CCTs for OHCA. This will utilise a previously published Emergency Medical Services (EMS) cost analysis toolkit and will take into account the costs incurred from use of a helicopter and the proportion of these costs currently covered by charities in the UK.

**Discussion:**

Prehospital critical care for OHCA is not universally available in many EMS. In the UK, it is variable and largely funded through public donations to charities. If this study demonstrates benefit from CCTs at an acceptable cost to the public or EMS commissioners, it will provide a rationale to increase funding and service provision. If no clinical benefit is found, the public and charities providing these services can consider concentrating their efforts on other areas of prehospital care.

**Trial registration:**

ISRCTN registry ID ISRCTN18375201.

## Background

### Prehospital treatment of out-of-hospital cardiac arrest

Sudden death due to out-of-hospital cardiac arrest (OHCA) remains a major health issue with an estimated 275,000 cardiac arrests in Europe each year [1]. Survival rates of between 5% and 38% have been reported, and have been linked to differences in prehospital treatment [1, 2]. Optimising care for patients suffering OHCA through early recognition and improved prehospital provider response times has been the focus of many emergency medical systems (EMS) over the last two decades [2, 3]. A range of different interventions has been studied [4, 5] but only early chest compressions [6, 7] and early defibrillation [2, 8] have been shown consistently to improve survival from OHCA. Despite a lack of clear evidence, many EMS have also established targeted dispatch of physicians and/or specialised critical care paramedics to OHCA; a concept referred to as prehospital critical care [9, 10]. These critical care teams (CCTs) attend cases of OHCA in addition to the standard ambulance response of paramedics trained in advanced life support (ALS). This has potential benefits, but also additional costs.

### Prehospital critical care for OHCA

The mechanisms by which outcomes might be improved through the presence of prehospital critical care practitioners include ALS interventions undertaken more efficiently, supplementation of existing protocols with enhanced experience and clinical judgment and an advanced level of post-arrest treatment [11]. In addition to these direct potential benefits of prehospital critical care, it might also allow for transport of patients with return of spontaneous circulation (ROSC) over greater distances, resulting in more patients receiving care at specialist centres, which has been shown to be beneficial [12]. There is little research addressing the concept of prehospital critical care in general, and in the context of OHCA specifically. A recently published systematic review on the impact of paramedic-delivered prehospital critical care did not identify any studies relating to OHCA [13]. A systematic review by Botker from 2009 examined the effect of physician-delivered prehospital critical care on OHCA outcomes and found a benefit, ‘based on limited evidence’ [14].

We have examined each of the five studies included in Botker’s review and have identified significant limitations in each of them. Small sample size [15] comparison of prehospital critical care with very limited basic life support [16] and study designs which did not control for significant confounding factors [16–19] make the interpretation and applicability of these findings problematic.

Olasveengen et al. acknowledged this lack of evidence regarding prehospital critical care for OHCA [20]. In 2009, the authors compared survival rates from OHCA with prehospital physician care (*n* = 232) and with paramedic ALS care (*n* = 741) in Norway. Data were collected prospectively and, after logistic regression to adjust for prognostic factors, no significant difference in outcomes was found.

In summary, there is no existing evidence to support paramedic-delivered prehospital critical care for patients with OHCA, while for physician-delivered prehospital critical care studies have shown mixed results, with the largest and most recent study failing to demonstrate any benefits [14, 20].

Research undertaken as a pilot study for this project examined the impact of the South West Ambulance Service NHS Foundation Trust’s (SWAST) CCT on survival from OHCA [21]. This retrospective database analysis compared survival to hospital discharge between 165 cases of OHCA attended by CCTs and 1686 cases attended by ALS-paramedics. While survival was significantly higher in the CCT group than the ALS-paramedic group (15.8% and 6.5%, respectively, *p* < 0.001), this was largely due to an imbalance in prognostic factors. After adjusting for these, using multiple logistic regression, there was no significant benefit from CCT attendance in this sample (OR 1.54, 95% CI 0.89–2.67, *p* = 0.13).

Currently, all EMS in the UK dispatch paramedics trained in advanced life support (ALS) to confirmed or suspected OHCA [3]. Prehospital critical care teams (CCTs) are utilised by some but not all NHS ambulance trusts, and their availability varies significantly across regions [9, 22]. This results in large variations in the care and resources available for OHCA, possibly reflecting the uncertainty regarding the clinical benefits of CCTs [9, 23].

### Economic considerations regarding prehospital treatment of OHCA

Research addressing cost-effectiveness of prehospital interventions is rare; a systematic review by Lerner in 2006 identified 32 publications, of which only two met criteria for high-quality economic evaluations [24]. A major obstacle to achieving such high-quality economic evaluations is the general paucity of high-level evidence of effectiveness, such as randomized controlled trials, in prehospital care [25]. Ten of the economic evaluations identified in the review address the factors which have been shown to improve survival from OHCA [24]. Table 1 summarises the interventions and cost per life saved found by studies included in the systematic review by Lerner et al [24]. It shows that existing interventions vary widely in their cost effectiveness, between individual interventions but also for the same intervention implemented in different circumstances. There is no publication to our knowledge that examines the provision of prehospital critical care for OHCA.

**Table 1 Tab1:** Key features of publications included by Lerner et al. [24] which address the cost-effectiveness of pre-hospital interventions for OHCA

Publications	Intervention	Incremental cost: Effectiveness $/Life saved
Ornato (1988) Jackobsson (1987)	Basic life support providers	$2,800–12,900
Hallstrom (1981) Nichol (1998) Jermyn (2000) Forrer (2002) Nichol (2003)	Defibrillation (pre-hospital provider and/or lay responders)	$7,800–$190,000
Nichol (1996)	Reducing EMS response time for OHCA	$262,700–$1,134,400
Urban (1981) Valenzuela (1990)	Advanced cardiac life support providers	$91,900–$181,000

### Aims and objectives

This prospective, observational study will describe the effect of CCTs on survival from OHCA, when compared to advanced-life-support (ALS), the current standard of prehospital care in the UK. In addition, we will describe the association between individual critical care interventions and survival. A stakeholder-focused cost analysis will describe the costs of CCTs for OHCA, in relation to public donations to charity and EMS commissioning.

## Methods

All included NHS ambulance trusts dispatch prehospital critical care teams to confirmed or suspected OHCA. While the CCTs will aim to attend most cases of OHCA, they will inevitably be unavailable for a proportion of these, due to already having been dispatched to another case of critical illness or injury, or the limitations imposed by operational duty hours and constrained funding. This results in a natural experiment where one group of patients is attended by the CCT and another is treated by ALS-trained paramedics. By comparing rates of survival to hospital discharge between these two groups, we will be able to measure the impact of prehospital critical care.

### Research sites

Study recruitment will take place in up to four NHS ambulance trusts. This combination will cover both rural and urban areas of the UK. All four ambulance trusts dispatch CCTs to OHCA by helicopter or in a rapid response vehicle, depending on time of day, weather and geographical considerations. We have shown in our previous research that prehospital critical care competencies are few in number, and of these few, only a fraction apply to prehospital critical care for OHCA [10]. We therefore anticipate that the team composition, critical care competencies and relevant protocols vary only slightly between the CCTs of the different trusts. These slight differences will not influence the results to any important degree regarding the impact of prehospital critical care (as a concept) on survival. We will compare CCT protocols prior to data collection, and the individual critical care interventions delivered for each case of OHCA will be recorded.

### Inclusion/ exclusion criteria

Patients will be 18 years or older and have suffered a non-traumatic OHCA. Inclusion criteria are adult cases of OHCA where EMS providers commenced cardiopulmonary resuscitation (CPR). Excluded are cases of OHCA due to trauma, drowning, electrocution and asphyxia or OHCA where no resuscitation attempts were made. Also excluded will be cases with incomplete documentation of matching variables. We will record all excluded cases and present the inclusion/exclusion process in the Utstein format [26].

### Data collection

We will analyse consecutive cases of adult OHCA, according to the inclusion and exclusion criteria. The study is planned to commence in September 2016 and continue for 18 months or until 6000 cases have been included, whichever occurs first.

Data collection will be from two data sources.

Ambulance trusts in the UK collect OHCA data routinely for quality assurance, independently of this research. These data are based largely on the Utstein variables and are recorded in regional databases. Participating ambulance trusts will provide data from their databases to the researchers. This first data source includes the following variables required for this research project:▪ Medical identifying number▪ Date and time▪ Location (public place, private location or nursing home)▪ Postcode of event (district level)▪ Age-group and gender of patient▪ Do Not Attempt Resuscitation order in place▪ EMS chest compressions▪ Witnessed event▪ Bystander CPR▪ Public access defibrillator used by bystander▪ Suspected cause▪ First EMS resource response time▪ First recorded cardiac rhythm▪ ROSC on arrival at hospital▪ Receiving hospital (if transported to hospital)▪ Survival to hospital discharge

In addition, we will collect data from the critical care teams (CCTs). Most CCTs keep a local electronic database of all cases where the CCT was requested, including the broad category of event (for example trauma, OHCA, medical). We will integrate a few additional data requests for every case identified as OHCA, specifically for this research:▪ Medical identifying number▪ Stand down prior to arrival at patient▪ CCT requested by ALS ambulance crew on scene▪ CCT members: Critical care paramedic and/or doctor▪ CCT response time▪ Interventions delivered during cardiac arrest▪ Interventions delivered after return of spontaneous circulation (ROSC)▪ Transport decisions and modalities▪ Provider decision to not provide full critical care in patient’s best interest

If no electronic CCT database exists, the required data will be collected on a simple paper form for each CCT OHCA case. The ambulance trust database and CCT data from each participating ambulance trust will be merged using the medical identifying number, creating the CCT and ALs groups.

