### Data analysis

In participating ambulance trusts, dispatch of CCTs is via a dedicated procedure which assesses all incoming 999 calls for signs of critical illness or injury. The decision to dispatch the CCT is generally based on a combination of clinical decision making of the dispatcher and the CCT as well as fixed dispatch criteria. In some cases EMS providers will request support from a CCT after arriving on scene. Our pilot study showed that the CCT is more likely to be dispatched to OHCAs with good prognostic factors, such as an OHCA with bystander CPR in a younger patient. The overall patient group attended by a CCT therefore has more favourable prognostic factors compared to the group attended by ALS-trained paramedics. To correct for this imbalance, we will match cases of the CCT group with controls of the ALS-trained paramedic group, using propensity score matching. This method of controlling for prognostic variables in observational data has been used successfully in OHCA research recently [27, 28]. We have shown that CCTs attend approximately 10% of all OHCA cases, resulting in a large pool of controls, allowing us to match multiple controls with each case (see step 2 below).

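### CCT attendance is traced only through CCT cases identified as OHCA, so an attended cohort patient filed under another category could be counted as an ALS control

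*Protocol article*

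**What the plan says.** All the steps are in the Data collection section of the protocol article.

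- The cohort comes from the ambulance trusts' OHCA databases. The listed variables run from the medical identifying number to "Receiving hospital (if transported to hospital)▪ Survival to hospital discharge". None records whether a CCT attended.
- Most CCTs keep a local database of every case for which they were requested, "including the broad category of event (for example trauma, OHCA, medical".
- The research items are added to part of that database: "We will integrate a few additional data requests for every case identified as OHCA, specifically for this research". They include the medical identifying number, stand-down before arrival, CCT response time and interventions. Where there is no electronic database, "the required data will be collected on a simple paper form for each CCT OHCA case".
- The two sources "will be merged using the medical identifying number, creating the CCT and ALs groups".

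The Data analysis section uses a different concept. The propensity model has CCT attendance as its dependent variable, and the matched groups are patients attended by a CCT and patients attended by ALS-trained paramedics alone.

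**The concern.** The exposure that is analysed is attendance. The exposure that is ascertained is narrower: attendance together with identification as OHCA on the CCT side. A patient who meets the first definition but not the second has no study record to link and falls into the ALS group by default.

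Two routes are plausible from the Data analysis section. CCT dispatch screens all emergency calls for critical illness or injury, so a team may be sent to a patient who arrests only later. Also, "In some cases EMS providers will request support from a CCT after arriving on scene", so ROSC can precede the team's arrival. In either case the event might be filed under a category other than OHCA.

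Matching cannot repair this, because the exposure label itself would be wrong and ROSC before CCT arrival is not among the listed covariates. The stand-down item deals only with the opposite error, a CCT that was requested but never reached the patient. The primary comparison of survival to discharge is at stake. The abstract says that a finding of no benefit could lead charities to concentrate on other areas of prehospital care.

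**Working it through.** **Inputs from the Sample size section.** 6000 patients, about 600 of them CCT, leaving 5400 ALS; control survival 7.5%; target difference about 4.5 points (12.0% against 7.5%); power 0.8; alpha 0.05 (taken as two-sided); 1:2 matching.

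**Inputs assumed, because the documents give none.** Share *f* of attended patients filed under another category: 2%, 5% or 10%. Survival *s* of those patients: equal to the CCT average, 25% or 35%.

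**The plan's own figure.** For two independent proportions, power = Φ[(δ − 1.96·SE₀)/SE₁].

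- SE₀ = √[0.09 × 0.91 × (1/600 + 1/1200)] = 0.01431
- SE₁ = √[0.12 × 0.88/600 + 0.075 × 0.925/1200] = 0.01529
- Power = Φ[(0.045 − 0.02805)/0.01529] = Φ(1.11) = 0.87

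The detectable difference at power 0.80 is 4.05 points. The stated 4.5 is thus not reproduced exactly but errs on the cautious side. It serves here only as a yardstick.

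**Effect of misfiling.** Let *m* = 600*f* patients move from CCT to ALS, carrying *ms* survivors.

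- Observed CCT survival = (600·p − ms)/(600 − m), where p is true CCT survival
- Observed ALS survival = (405 + ms)/(5400 + m), since 5400 × 0.075 = 405

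*Worked case, f = 5%, s = 25%:* m = 30 and ms = 7.5. The ALS rate becomes 412.5/5430 = 7.60%.

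- True +4.5 points: CCT (72 − 7.5)/570 = 11.32%; difference +3.7 points; power 0.71 with 570 CCT cases and 1:2 matching.
- No true effect: CCT (45 − 7.5)/570 = 6.58%; difference −1.0 point.

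| Misfiled | Survival of misfiled | Observed, true +4.5 (power) | Observed, true 0 |
|---|---|---|---|
| 2% | 25% | +4.2 (0.81) | −0.4 |
| 5% | 25% | +3.7 (0.71) | −1.0 |
| 10% | 25% | +2.9 (0.49) | −2.1 |
| 2% | 35% | +4.0 (0.78) | −0.6 |
| 5% | 35% | +3.1 (0.58) | −1.6 |
| 10% | 35% | +1.6 (0.21) | −3.4 |

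*Misfiling unrelated to prognosis:* with f = 10% and s = 12%, CCT stays at 12.0% and ALS becomes (405 + 7.2)/5460 = 7.55%. The difference is 4.45, a loss of 0.05 points. With no true effect there is no shift.

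These figures give the misfiled patients the same weight among the controls as they have in the whole ALS pool. If instead all 30 in the worked case were chosen among 1140 matched controls, control survival would be 7.5% × 1110/1140 + 25% × 30/1140 = 7.96%, and the observed difference 11.32 − 7.96 = 3.4 points. Most of the loss comes from survivors leaving the CCT group.

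**The case against.** The strongest reply is that the text shows a gap but no directional bias. A reader might infer that the CCT's category depends on the patient's condition when the team arrives, so that patients with early ROSC are filed as medical and survivors drain systematically into the ALS group. Nothing in the article says so. The category describes the event and is held for every request. Stand-down before arrival is itself an item for OHCA-identified cases, so some cases carry that label although the team never met the patient. The items also include "Interventions delivered after return of spontaneous circulation (ROSC" and whether the crew on scene asked for the CCT, so many patients with ROSC or a late request are evidently expected among the OHCA cases. This part of the reply stands. It shows that not all such patients would be missed, not that none would be.

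A reader might also infer that most of the target difference could vanish. Suppose 30% of CCT patients had ROSC before arrival, 30% of them survived, and half were misfiled. CCT survival would then fall from 12.0% to (72 − 27)/510 = 8.8%. But that assumes 54 of the 72 survivors come from those 180 patients, leaving 18 survivors among the other 420 (4.3%), below the 7.5% assumed for controls. It is not a credible planning figure.

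The article also does not name who identifies a case as OHCA, and the merge sentence speaks of CCT data without restriction. The CCT's own category is the natural reading, given the preceding sentence and the paper-form rule, but it remains a reading.

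Finally, linkage checks may be left to a fuller protocol. The absence of a check would be no fault in itself. The point here is that the article states an ascertainment rule, and that rule is narrower than the exposure it defines.

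**Conclusion.** The gap holds as a matter of text: under the stated rule, an attended cohort patient not identified as OHCA by the CCT could be analysed as an ALS control. This should be corrected because correction is cheap and aligns ascertainment with the attendance-based exposure, not because a bias has been shown.

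Size and direction are unknown. If filing is unrelated to prognosis, the effect is negligible. If misfiling is commoner after early ROSC, the comparison is biased against the CCT; over the assumed 2% to 10% misfiled with 25% or 35% survival, a true +4.5 points would be observed as +4.2 down to +1.6. Those inputs are assumptions, and the documents support no particular value in the range.

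**What to change.** Define exposure as CCT arrival at the patient. Establish it by linking every trust-database OHCA case to the complete CCT activation log, whatever category the CCT gave the event. Collect the study items for every linked case, completing them retrospectively where the event was not labelled OHCA. At paper-form sites, complete a form for each activation that links to a trust OHCA record. State who identifies a case as OHCA, and report the number of cases that the two sources label differently.

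The article says that most CCTs already log all requests, so the main cost is a wider extract and some retrospective completion of intervention data. The change does depend on identifiers being held on non-OHCA CCT records. Their availability should be confirmed before data collection, especially at sites without an electronic database, where the completeness of any activation log is unknown.

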### Data analysis

In participating ambulance trusts, dispatch of CCTs is via a dedicated procedure which assesses all incoming 999 calls for signs of critical illness or injury. The decision to dispatch the CCT is generally based on a combination of clinical decision making of the dispatcher and the CCT as well as fixed dispatch criteria. In some cases EMS providers will request support from a CCT after arriving on scene. Our pilot study showed that the CCT is more likely to be dispatched to OHCAs with good prognostic factors, such as an OHCA with bystander CPR in a younger patient. The overall patient group attended by a CCT therefore has more favourable prognostic factors compared to the group attended by ALS-trained paramedics. To correct for this imbalance, we will match cases of the CCT group with controls of the ALS-trained paramedic group, using propensity score matching. This method of controlling for prognostic variables in observational data has been used successfully in OHCA research recently [27, 28]. We have shown that CCTs attend approximately 10% of all OHCA cases, resulting in a large pool of controls, allowing us to match multiple controls with each case (see step 2 below).

Propensity score matching will involve the following steps [29]:We will run a logistic regression with CCT attendance as the dependent variable. Prognostic factors for both survival to hospital discharge and CCT dispatch will be covariates. They will include age and gender of the patient, the cause and location of OHCA, whether it was witnessed, bystander CPR, ambulance response time, first recorded rhythm and distance from CCT base. This will allow us to calculate a propensity score for each patient - the probability of the patient receiving CCT treatment.We will then match each CCT case with ALS-trained paramedic cases of OHCA, with similar propensity scores. This will be done using nearest neighbour matching within a specified calliper distance - the ‘greedy algorithm’ assigns controls with similar propensity scores to each case. To qualify as 'matching' the propensity score of potential controls needs to be within 0.2 of the pooled standard deviation of the logit of the propensity score [30]. This reduces the risk of bias from matching controls to cases whose propensity scores differ too much. To optimise available data, we will match each CCT case with up to five ALS-paramedic controls whose propensity scores are within the defined caliper, accepting varying numbers of controls per case. Each control will only be available for matching once and then will be removed from the control pool [31].We will compare the matched CCT and ALS-paramedic groups to verify that prognostic factors are balanced between the groups.We will analyse for statistically significant differences in survival to hospital discharge between the groups (see also ‘3.2.5 data analysis’).

The matching process will result in two groups of OHCA patients: an intervention group that has been attended by a CCT in addition to the usual ambulance response, and a control group that has been attended by ALS-trained paramedics alone. We will compare the primary outcome of survival to hospital discharge between OHCA attended by the CCT and OHCA attended by ALS-trained paramedics. We will conduct multivariable logistic regression analyses for the full cohort and conditional logistic regression for the propensity score matched groups. We will also undertake subgroup analysis for witnessed OHCA with shockable rhythm, with the hypothesis that any potential benefit of CCT attendance will be more pronounced. There is a possibility that any observed benefit from CCT care is due partially to CCTs conveying more patients to a cardiac centre, bypassing nearer hospitals. We will therefore also compare the secondary outcome of survival to hospital admission.

In addition, we will describe the frequency of prehospital critical care interventions delivered by the CCTs for OHCA. We will then undertake logistic regression analysis including known predictors of survival, with the individual critical care interventions as independent variables and survival to hospital discharge as a dependent variable. We estimate that there will be enough survivors of OHCA to allow multiple logistic regression with up to ten variables (estimated 100 survivors, with 10 outcomes per variable). However, should this not be possible, we will describe frequency of critical care interventions occurring during OHCA treatment, which will be useful information when interpreting the overall results of this project.

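### The CCT group is defined by actual attendance, which is settled after cohort entry and can depend on the patient's course, so the primary comparison can be biased in either direction

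*Protocol article*

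**What the plan says.** All references are to the Methods of the protocol article.

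- **Cohort entry** (Inclusion/ exclusion criteria): adult non-traumatic arrests in which EMS started CPR.
- **Exposure** (Data analysis): "We will run a logistic regression with CCT attendance as the dependent variable". After matching, the CCT arm consists of cases that a CCT reached on top of the normal response, and the comparator is "a control group that has been attended by ALS-trained paramedics alone".
- **Routes into and out of attendance after the call**: the CCT data include "Stand down prior to arrival at patient" and "CCT requested by ALS ambulance crew on scene" (Data collection). Data analysis confirms that the second happens: "In some cases EMS providers will request support from a CCT after arriving on scene".
- **Adjustment** (Data analysis): the propensity model contains "age and gender of the patient, the cause and location of OHCA, whether it was witnessed, bystander CPR, ambulance response time, first recorded rhythm", together with distance from the CCT base. These are described as factors prognostic for survival and for CCT dispatch, although the modelled event is attendance.
- **Rationale** (opening paragraph of Methods): non-attendance is put down to other calls, duty hours and funding, and the comparison is called a natural experiment.

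**The concern.** The CCT comes in addition to the ambulance crew, so there is an interval between cohort entry and the moment at which attendance is settled. What happens to the patient in that interval can decide the group. A team may be stood down because resuscitation has ended or because the patient has already recovered a pulse. A crew may ask for a team because ROSC has been achieved or because the arrest is refractory. In each case group membership carries prognostic information that did not exist at cohort entry.

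The natural-experiment argument covers only reasons for non-attendance that have nothing to do with the patient. It does not mention the two routes that the article itself records.

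The estimate feeds the cost analysis and commissioning advice. The abstract says that a benefit would support more funding and that a null result could lead charities to put their efforts elsewhere. A spurious result in either direction therefore matters.

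**Working it through.** **The plan's own figure, as a yardstick.** Inputs from Sample size: 600 CCT cases, one-to-two matching (1,200 controls), 7.5% control survival, a 4.5-point difference (12.0% against 7.5%), alpha 0.05, power 0.8. A two-sided test of two proportions with pooled variance gives power 0.866. About 496 CCT cases would suffice for 0.80, and with 600 the detectable difference is about 4.1 points. The stated 4.5 is slightly conservative, which is not at issue here.

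**Order of events**

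1. 999 call, with possible CCT dispatch.
2. First EMS contact. Rhythm and response time are known, so every propensity covariate is now fixed.
3. EMS start CPR: cohort entry.
4. The patient's course under ALS. A crew request can only come after the crew has arrived, and a stand-down can come at any time before the CCT arrives.
5. CCT arrival: exposure is settled.

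No listed covariate describes step 4. Balance checks on the listed covariates could look good while the groups still differ in what happened there. The full-cohort regression, the witnessed shockable subgroup and survival to admission are described for the same CCT and ALS groups, so none of them is a check on this.

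**Illustration under no true CCT effect.** From Sample size: 6,000 patients, 600 attended, 7.5% overall survival (450 survivors). The shares and survival rates of the affected cases are assumptions, because the documents give none. The survival rates should be read as what remains after matching.

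*Stand-downs counted as ALS.* With D dispatched, s = D − 600 stood down and survival p among them:

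- CCT rate = (0.075 × D − p × s) / 600
- ALS rate = (0.075 × (6,000 − D) + p × s) / 5,400

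For D = 700 and p = 0: CCT = 52.5/600 = 8.75%, ALS = 397.5/5,400 = 7.36%, difference +1.4 points.

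*Crew requests counted as CCT.* With a share f of the 600 and survival p among them:

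- CCT rate = (1 − f) × 0.075 + f × p
- ALS rate = (450 − 600 × CCT rate) / 5,400

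For f = 10% and p = 25%: CCT = 9.25%, ALS = 394.5/5,400 = 7.31%, difference +1.9 points.

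*Rejection rate.* Normal approximation, two-sided 5%, SE = √(0.075 × 0.925 × (1/600 + 1/1,200)) = 0.0132.

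| Assumed event | Survival in those cases | CCT | ALS | Difference (points) | Rejection |
|---|---|---|---|---|---|
| 100 stood down (of 700) | 0% | 8.75% | 7.36% | +1.4 | 18% |
| 100 stood down (of 700) | 20% (early ROSC) | 5.42% | 7.73% | −2.3 | 42% |
| 150 stood down (of 750) | 0% | 9.38% | 7.29% | +2.1 | 35% |
| 150 stood down (of 750) | 20% | 4.38% | 7.85% | −3.5 | 75% |
| 200 stood down (of 800) | 0% | 10.00% | 7.22% | +2.8 | 56% |
| 200 stood down (of 800) | 20% | 3.33% | 7.96% | −4.6 | 94% |
| 5% crew requests | 25% (post-ROSC) | 8.38% | 7.40% | +1.0 | 11% |
| 10% crew requests | 25% | 9.25% | 7.31% | +1.9 | 32% |
| 20% crew requests | 25% | 11.00% | 7.11% | +3.9 | 84% |
| 5% crew requests | 2% (refractory) | 7.23% | 7.53% | −0.3 | 6% |
| 10% crew requests | 2% | 6.95% | 7.56% | −0.6 | 8% |
| 20% crew requests | 2% | 6.40% | 7.62% | −1.2 | 15% |

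The result also depends on the assumed survival. With 100 stand-downs it is +1.0 at 2% survival and −4.2 at 30%. With 10% crew requests it is +3.1 at 35% survival. If stood-down patients survive at the average 7.5%, the difference is zero.

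**The case against.** - **Allocation of stand-downs.** A reader might infer that the plan sends stood-down cases to the ALS group. It does not say so. Data collection forms the groups by merging trust data with CCT records that carry the stand-down flag, without assigning flagged cases. The inference rests on the Data analysis wording that controls were attended by ALS paramedics alone. This objection stands, and the allocation needs stating.
- **Silence in a condensed article.** Both flags are collected specifically for this research, and a fuller plan may use them. That is fair as to the flags. It does not remove the point, because attendance as the exposure is a rule that the article itself fixes.
- **Direction.** A reader might infer immortal-time bias in favour of the CCT. The documents do not support a one-sided reading: early-ROSC stand-downs and refractory-arrest requests push the other way. Only the need to be still under resuscitation, or to have ROSC, when the CCT arrives is immortal time in the strict sense. Crew request is confounding by indication.
- **Size.** Some stand-downs may be for competing calls, which is harmless unavailability. Arrests without a resuscitation attempt are excluded, so patients found dead and not resuscitated never enter. Matching on rhythm, witnessed status, bystander CPR, age and response time will absorb part of any raw survival difference. All of this stands: the propensity score cannot fully remove the bias, which is not to say that it removes none.
- **Estimand.** The stated aim is the effect of CCT care compared with ALS. An analysis by dispatch answers a somewhat different question, so it belongs beside the attendance comparison and need not replace it.

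**Conclusion.** The point holds in limited form. The exposure rule lets events after cohort entry decide the group, the listed covariates cannot capture those events, and no stated analysis tests for the effect. The primary odds ratio can therefore be biased with no true effect.

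Neither the size nor the net direction can be derived from the documents. At the moderate assumed shares (100 to 150 stand-downs, or 10% crew requests), mechanisms favouring the CCT give roughly +1 to +2 points. In the other direction, 100 early-ROSC stand-downs give about −2 points and 10% refractory-arrest requests about −0.6. Larger shares reach the order of the 4.5-point target. These figures assume 7.5% survival overall, covariates otherwise balanced and, for stand-downs, allocation to ALS.

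The conclusion that the study will show a spurious CCT benefit is not supported. Nor is the conclusion that the attendance comparison must be abandoned.

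**What to change.** 1. State which group stood-down cases and crew-requested cases belong to in the attendance comparison.
2. Pre-specify, alongside that comparison, an analysis with exposure defined as CCT dispatch from the 999 call. Stood-down dispatches stay in the CCT group, crew-requested cases count as not dispatched, and the propensity model predicts dispatch. Crew-requested cases should not be dropped from this analysis, because that would itself condition on an event after cohort entry.
3. Add a sensitivity analysis of the attendance comparison without crew-requested cases.
4. Report how often each event occurred, and qualify the conclusion if the analyses disagree.

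**Cost.** Plan wording and a few extra model runs, using flags already listed in Data collection. The dispatch effect is diluted by stand-downs and by later requests in the comparison group, and it answers a slightly different question from attendance. Services without an electronic database use a paper form for each CCT arrest case, so they must be told to complete it for stood-down cases too. Matching on still being under resuscitation at CCT arrival would be more direct, but the listed fields include no time of ROSC or of termination.
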